# Acute cholecystitis in high risk surgical patients: percutaneous cholecystostomy versus laparoscopic cholecystectomy (CHOCOLATE trial): Study protocol for a randomized controlled trial

**DOI:** 10.1186/1745-6215-13-7

**Published:** 2012-01-12

**Keywords:** Acute cholecystitis, laparoscopic cholecystectomy, percutaneous cholecystostomy, percutaneous drainage

## Abstract

**Background:**

Laparoscopic cholecystectomy in acute calculous cholecystitis in high risk patients can lead to significant morbidity and mortality. Percutaneous cholecystostomy may be an alternative treatment option but the current literature does not provide the surgical community with evidence based advice.

**Methods/Design:**

The CHOCOLATE trial is a randomised controlled, parallel-group, superiority multicenter trial. High risk patients, defined as APACHE-II score 7-14, with acute calculous cholecystitis will be randomised to laparoscopic cholecystectomy or percutaneous cholecystostomy. During a two year period 284 patients will be enrolled from 30 high volume teaching hospitals. The primary endpoint is a composite endpoint of major complications within three months following randomization and need for re-intervention and mortality during the follow-up period of one year. Secondary endpoints include all other complications, duration of hospital admission, difficulty of procedures and total costs.

**Discussion:**

The CHOCOLATE trial is designed to provide the surgical community with an evidence based guideline in the treatment of acute calculous cholecystitis in high risk patients.

**Trial Registration:**

Netherlands Trial Register (NTR): NTR2666

## Background

Acute calculous cholecystitis (ACC) is a frequently encountered disease in the general surgical practice. In young, otherwise healthy patients laparoscopic cholecystectomy (LC) is the treatment of choice [1]. In elderly patients with major comorbidity and seriously ill patients, especially those already admitted to an intensive care unit, percutaneous cholecystostomy (PC) seems preferable since acute LC in these patients can result in serious morbidity (up to 41%[2-7]) and mortality (up to 4.5%[2-6,8]). But there is a remaining subgroup of patients who can be defined as "high risk patients" based on their comorbidity or disease severity but do not fit in either of the two afore-mentioned categories.

Both LC and PC are often used in this subgroup of patients but clear selection criteria for either treatment are lacking and a number of questions regarding the safety and efficacy of PC remain.

In the Dutch guidelines for the treatment of gallstone disease [9] PC is indicated as a useful treatment option in patients deemed unfit for surgery but it is left open to discussion whether routine use of PC has additional value over antibiotic treatment in the therapy of ACC in the general population. Little evidence is provided to support this statement.

Most studies in the current literature addressing PC as a therapeutic option in ACC in high risk patients are retrospective with limited population sizes. Success rates are fairly high, but mortality rates of PC (range 4-12.7%[6]) are higher than those for LC. This could be attributed to selection bias as it is to be expected that those patients treated with PC were in a worse clinical condition than those treated with LC.

A systematic review conducted in 2007[6] analyzed the safety and efficacy of PC in elderly and critically ill patients. The review identified no clinical trials comparing PC with LC and the included studies were mostly retrospective and involved small patient populations. With a success rate of 91% in patients with confirmed ACC and a procedure related mortality of 0.4% results of PC seemed promising. The overall mortality was 12.7% and the overall complication rate was reported to be 6.2%. Complication rates were not included in more than half of the studies thus leading to an underestimation of the actual complication rate.

We performed a retrospective review of all patients undergoing PC for acute calculous cholecystitis between January 2009 and June 2010 [10]. A total of 27 patients were included with a median age of 83 years. PC was performed because of either comorbidity/age or duration of symptoms. The success rate was 92.6% (N = 25) but the complication rate was 22.2% (N = 6). The overall mortality rate was 14.8% (n = 4) and the procedure related mortality rate 3.7% (N = 1). With a mean follow-up of eight weeks three patients developed recurrent cholecystitis and four patients underwent an interval cholecystectomy.

Current literature and data from our own clinical experience fail to answer the question which therapy is the best option in ACC in high risk patients. At present both treatment strategies are used in this patient category and the preference and expertise of the responsible surgeon or the general opinion within the hospital usually determines the choice of treatment.

The CHOCOLATE trial is designed to assess which treatment modality is best suited for high risk patients with ACC, with the aim to prove superiority of the laparoscopic cholecystectomy.

## Methods

### Design

The CHOCOLATE trial is a randomised controlled, open, parallel, superiority multicenter study. Patients will be randomly allocated to undergo either laparoscopic cholecystectomy or percutaneous drainage.

The aim of this study is to test the hypothesis that laparoscopic cholecystectomy will lead to a reduction in morbidity and mortality compared to percutaneous drainage in high risk patients with acute calculous cholecystitis.

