### Primary & Secondary endpoints

The primary endpoint is a composite endpoint of all major morbidity, re-intervention and mortality. Table 1 provides an overview of the definitions. Complications occurring during the first 30 days subsequent to randomisation and need for reintervention and mortality during the one year follow-up period will be compared.

**Table 1 T1:** Definitions of the primary endpoint.

Endpoint	Definition
*Complications*	
Intra-abdominal abscess	Fever and/or elevated CRP/WBC and intra-abdominal fluid collection on CT-imaging or ultrasound.
Biliary injury	All injuries of the intra- and extrahepatic biliary ducts including leakage of the biliary tree*.
Bleeding	Drop in haemoglobin level requiring transfusion and/or reintervention.
Pneumonia	Coughing or dyspnoea, radiography with infiltrative abnormalities, elevated infection parameters and positive sputum culture.
Myocardial infarction	Symptomatic elevated cardiac enzymes and abnormalities on electrocardiography or cardiac ultrasound.
Cerebrovascular	(Temporary) loss of function of any body part or sense caused by cerebral ischemia or bleeding, proven on cerebral CT imaging.
Thrombo-embolic	Symptomatic deep venous thrombosis or pulmonary embolism, radiologically proven.
*Need for re-intervention*	Relaparoscopy, laparotomy, ERCP, intervention radiology, readmission
*Mortality*	

CRP - C-Reactive Protein; WBC - White Blood Cell count; CT - computed Tomography; ERCP - Endoscopic Retrograde Cholangiopancreaticography

* Type A: leakage of the minor hepatic ducts or cystic duct. Type B: leakage of common bile duct (CBD) without stricture - Type C: stricture of the CBD without bile leakage - Type D: complete transection of the CBD with or without resection of a part of it [11].

The secondary endpoints include all individual components of the primary endpoint and in addition all minor complications including wound infection, bleeding without need for transfusion or intervention and urinary tract infection, difficulty of cholecystectomy (as scored by VAS 1-10), total length of hospital stay, emergency room visits for related medical problems, re-admissions, duration of hospital and intensive care stay and total (direct and indirect) costs.

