## Statistical aspects

### Sample size calculation

The rates for the primary endpoint: major morbidity, re-intervention and mortality for PC were 6.2, 13.1 and 12.7% respectively in the review and 22.2, 18.5 and 14.8% in our own series. We believe that the 6.2% complication rate in the review is an underestimation of the actual rate, but our own value of 22.2% was based on a retrospective, selected group of patients to undergo PC mostly because of their comorbidity. In these patients the complication rate may very well be higher than in the intended population of the CHOCOLATE trial. We therefore chose to combine both complication rates and use the mean value for our sample size calculation: 14.2%.

Morbidity rates for LC in high risk patients vary greatly in current literature and are mainly based on small, retrospective populations. Mortality rates are described to be around 4.5%. In our own series the complication rate was 13.6% and the mortality rate was 4.3%.

Our endpoint comprises major complications and mortality. These rates cannot be simply added to each other since mortality is in most case associated with major complications. We therefore chose to add intervention rates and complication rates and add up a hypothetical 1% for mortality to ensure that no cases positive for the primary endpoint were missed.

A decrease of the primary endpoint from 28.3% (PC group) to 14.6% (LC group) with power 80%, alpha two-sided 5%, Fisher exact, two proportions, 1:1 randomization can be demonstrated by randomizing 2 × 140 patients (PS Power and Sample Size Calculations, version 2.1.30, February 2003). With an expected loss to follow up of 1%, a total of 284 patients will have to be included in the trial.

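### The stated hypothesis names morbidity and mortality, but the primary test also counts re-intervention, which supplies about 13.1 of the 13.7 planned percentage points

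*Protocol article*

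**What the plan says.** The Design section gives the aim as testing that "laparoscopic cholecystectomy will lead to a reduction in morbidity and mortality compared to percutaneous drainage". Re-intervention is not mentioned there.

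The section on primary and secondary endpoints says: "The primary endpoint is a composite endpoint of all major morbidity, re-intervention and mortality". Table 1 sets need for re-intervention under its own heading, apart from complications, and defines it as "Relaparoscopy, laparotomy, ERCP, intervention radiology, readmission". On timing, the same section says: "Complications occurring during the first 30 days subsequent to randomisation and need for reintervention and mortality during the one year follow-up period will be compared". All components are also listed as secondary endpoints.

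The sample size section again treats the three components separately. It gives percentages that "for PC were 6.2, 13.1 and 12.7% respectively in the review and 22.2, 18.5 and 14.8% in our own series" and takes the average of the two PC complication rates: "use the mean value for our sample size calculation: 14.2" per cent. For LC it says: "In our own series the complication rate was 13.6% and the mortality rate was 4.3" per cent; it also cites a literature mortality of around 4.5%. It prints no LC re-intervention rate. It describes the endpoint as made up of major complications and mortality, and then builds the rate by adding intervention and complication rates plus a hypothetical 1% for mortality. The result is "A decrease of the primary endpoint from 28.3% (PC group) to 14.6% (LC group) with power 80" per cent, at two-sided 5% and 140 patients per arm.

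**The concern.** A significant primary result would be read against the hypothesis in the Design section. That hypothesis concerns morbidity and mortality, whereas the endpoint tested has a third component that the article itself keeps distinct from complications and from death. If most of the planned difference lies in that third component, the trial can succeed as designed without any evidence on what its hypothesis names.

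The distinction matters to users of the result. Fewer deaths and major complications is one message; fewer later procedures and readmissions is another. The section on premature termination says that treatment policy will be based on this trial, so the conclusion should state which of the two the primary test can support.

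**Working it through.** **Inputs** (sample size section unless noted)
- PC: complications 14.2%, the mean (6.2 + 22.2)/2; re-intervention 13.1% from the review.
- LC: complications 13.6% from the authors' own series; no re-intervention rate printed.
- Mortality: a hypothetical 1% added to the composite.
- 140 per arm, two-sided 5%. The Analyses section names the chi-square test; the sample size section names Fisher's exact test.

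**1. Reproduce the planned rates.**
- PC: 14.2 + 13.1 + 1 = 28.3%, as printed.
- LC: 13.6 + 0 + 1 = 14.6%, as printed. The zero for re-intervention is inferred from this sum.

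**2. Reproduce the planned power.** The usual two-proportion formula without continuity correction gives 140 per arm for 28.3% v 14.6%. Exact binomial enumeration of the chi-square test at 140 per arm gives 80.5% power.

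**3. Decompose the planned difference.** 28.3 − 14.6 = 13.7 points:
- re-intervention 13.1 − 0 = 13.1 (13.1/13.7 = 96%);
- complications 14.2 − 13.6 = 0.6;
- mortality 1 − 1 = 0.

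**4. Hold death-or-major-complication equal and let only re-intervention differ.** Set death-or-major-complication at 13.6 + 1 = 14.6% in both arms and PC re-intervention at 13.1%. Let r be LC re-intervention.
- Additive, as in the plan: PC 14.6 + 13.1 = 27.7%; LC 14.6 + r.
- Independent: PC 1 − 0.854 × 0.869 = 25.8%; LC 1 − 0.854 × (1 − r).

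Chance that the composite test (chi-square, exact enumeration) favours LC:

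| LC re-intervention | Additive | Independent |
|---|---|---|
| 0% (implied by the plan) | 27.7 v 14.6%: 77% | 25.8 v 14.6%: 65% |
| 3% (assumed) | 27.7 v 17.6%: 53% | 25.8 v 17.2%: 42% |
| 5% (assumed) | 27.7 v 19.6%: 36% | 25.8 v 18.9%: 28% |

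With Fisher's exact test the 77% becomes about 73%.

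Overlap can also be varied directly. Take 14.2 + 1 = 15.2% in both arms and LC re-intervention 0%. If a quarter of PC re-interventions fall in patients already counted, the PC rate is 15.2 + 0.75 × 13.1 = 25.0% and the figure is 54%. If half do, it is 15.2 + 0.5 × 13.1 = 21.75% and 29%.

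**5. Power for what the hypothesis names.**
- At the planning values, complications plus 1%: 15.2% v 14.6%, power about 5%.
- If the cited mortality rates were fully additive to complications: 14.2 + 12.7 = 26.9% v 13.6 + 4.5 = 18.1%, power about 42%. This is an upper case, since the article itself says most deaths occur in patients with major complications.

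**The case against.** Several points on the other side stand.

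- **The endpoint is not in doubt.** The abstract, the endpoint section, Table 1 and the opening of the sample size section all name re-intervention. The Design sentence can be read as a loose summary. That is fair, but the sample size section repeats the short form in the paragraph that adds intervention rates, and the article's own tables and rates keep morbidity and re-intervention apart.
- **The percentages in step 4 are not false-positive rates.** A reader might infer that the test rejects a true null far more often than 5%. The article prints no null hypothesis; the formal null of the test is equal composite proportions. That null is false in every scenario of step 4, so rejection there is correct power for the composite.
- **Most trials need not be won on re-intervention alone.** A reader might infer this as a general statement. It holds only near 13.1% v 0% with little overlap. The zero is inferred, readmission after LC also counts, and overlap is built in, since Table 1 allows bleeding to be defined by need for re-intervention. Three of the four cells with LC at 3% or 5% are below one half.
- **The zero for mortality is a placeholder.** A reader might infer that the trial plans for no mortality effect. The 1% is called hypothetical and was chosen because of overlap with complications; cited mortality is 12.7% and 14.8% for PC against about 4.5% and 4.3% for LC.
- **Testing order is commonly left to the analysis plan**, which is not shown. The components are already secondary endpoints, so a composite driven by re-intervention would be visible. The absence of a gatekeeping rule is therefore no finding.

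What remains is the disagreement between two printed statements and its effect on what a significant result may be said to show.

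**Conclusion.** The mismatch holds, and it affects the claim rather than the validity of the test. The hypothesis as worded concerns morbidity and mortality. The planned difference in the primary endpoint is about 96% re-intervention by the article's own construction, and the stated 80% power belongs to the composite only.

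The size depends on three assumptions: LC re-intervention of 0% (implied, not printed), no overlap between components, and complications and mortality equal in both arms. Under these the composite would favour LC in about 77% of trials. The figure is 65% under independence, and about 28% to 53% with LC re-intervention at an assumed 3% to 5%. Power for death-or-major-complication lies between about 5% at the planning values and about 42% in the fully additive mortality case.

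The documents do not support a charge of inflated type I error, nor a prediction that the trial will misreport its result. They do support correcting the hypothesis and limiting the claim. The correction is worth making because it is nearly free and changes what the trial may conclude.

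**What to change.** 1. In the Design section, restate the hypothesis as a reduction in the composite of major complications, re-intervention and mortality. Make the same correction where the sample size section describes the endpoint as complications and mortality only.
2. State that the 80% power applies to that composite only.
3. Name death-or-major-complication (Table 1 complications plus mortality) as a secondary analysis. Let any claim that LC reduces morbidity and mortality rest on that result, not on the composite alone. If only the composite is significant, describe the finding as a lower composite and show the components.

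Testing the secondary endpoint only after a significant composite is one option, not a requirement.

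The cost is wording and one further analysis of data already collected, with no extra patients and no alpha taken from the primary test. The article reports 34 patients enrolled, so the change can precede any final results. The downside is a narrower stated claim, with the low power for morbidity and mortality made explicit.

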### Primary & Secondary endpoints

The primary endpoint is a composite endpoint of all major morbidity, re-intervention and mortality. Table 1 provides an overview of the definitions. Complications occurring during the first 30 days subsequent to randomisation and need for reintervention and mortality during the one year follow-up period will be compared.

**Table 1 T1:** Definitions of the primary endpoint.

Endpoint	Definition
*Complications*	
Intra-abdominal abscess	Fever and/or elevated CRP/WBC and intra-abdominal fluid collection on CT-imaging or ultrasound.
Biliary injury	All injuries of the intra- and extrahepatic biliary ducts including leakage of the biliary tree*.
Bleeding	Drop in haemoglobin level requiring transfusion and/or reintervention.
Pneumonia	Coughing or dyspnoea, radiography with infiltrative abnormalities, elevated infection parameters and positive sputum culture.
Myocardial infarction	Symptomatic elevated cardiac enzymes and abnormalities on electrocardiography or cardiac ultrasound.
Cerebrovascular	(Temporary) loss of function of any body part or sense caused by cerebral ischemia or bleeding, proven on cerebral CT imaging.
Thrombo-embolic	Symptomatic deep venous thrombosis or pulmonary embolism, radiologically proven.
*Need for re-intervention*	Relaparoscopy, laparotomy, ERCP, intervention radiology, readmission
*Mortality*	

CRP - C-Reactive Protein; WBC - White Blood Cell count; CT - computed Tomography; ERCP - Endoscopic Retrograde Cholangiopancreaticography

* Type A: leakage of the minor hepatic ducts or cystic duct. Type B: leakage of common bile duct (CBD) without stricture - Type C: stricture of the CBD without bile leakage - Type D: complete transection of the CBD with or without resection of a part of it [11].

The secondary endpoints include all individual components of the primary endpoint and in addition all minor complications including wound infection, bleeding without need for transfusion or intervention and urinary tract infection, difficulty of cholecystectomy (as scored by VAS 1-10), total length of hospital stay, emergency room visits for related medical problems, re-admissions, duration of hospital and intensive care stay and total (direct and indirect) costs.

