### Treatment protocol

All patients presenting with suspected ACC in the emergency department will undergo the standard laboratory work-up and an arterial blood gas analysis. An ultrasound of the abdomen will be performed to confirm the diagnosis. If the findings on ultrasound examination are inconclusive, a contrast enhanced CT-scan of the abdomen will be performed.

When patients are eligible for inclusion and informed consent is obtained randomisation will take place. The allocated treatment has to be performed within 24 hours after randomisation. Figure 1 demonstrates the study outline for included patients.

Group A: Laparoscopic cholecystectomy

LC will be performed by the four trocar technique with transsection of the cystic duct and cystic artery after reaching the critical view of safety as described in the Dutch Guidelines for the treatment of gallstone disease [9]. LC will be performed by a surgeon trained and experienced in laparoscopic surgery defined as > 100 laparoscopic procedures on a yearly basis.

Patients may receive prophylactic antibiotics according to the local hospital protocol.

Antibiotic therapy will not be routinely continued post-operatively unless the performing surgeon has strong indications to do so (such as (imminent) sepsis or hemodynamic instability). In these cases the primary investigator will be notified and the indications have to be well documented.

Group B: Percutaneous drainage

PC will be performed by either ultrasound- or CT-guided percutaneous drainage using an 8.5 French maclock drain. Since there is no consensus in the current literature [9,13] both the transhepatic and transperitoneal routes are allowed and which route is the safest in the individual patient is to be judged by the performing radiologist.

Successful PC is defined as resolution of symptoms and fever and normalization of C-Reactive protein and white blood count. Failure to thrive, defined as clinical deterioration, persisting fever, or increasing infection parameters < 48 hours despite accurate drain position and function will lead to LC.

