Patients will be discharged with the drain in place. The drain will be left in situ during a period of three weeks, after which contrast-imaging of the drain will be performed prior to removal to assess whether the drain is still located in the gallbladder and whether there is a patent cystic duct. Patients undergoing PC will not be treated with antibiotics unless the patient is septic with (imminent) hemodynamic instability.

When patients in either group develop an infectious complication antibiotic therapy can be started. All events will be recorded.

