### Analyses

All patients will be analysed according to the intention to treat approach. Baseline balance will be assessed based on the following patient factors: APACHE-II score, sex, age, duration of symptoms, previous abdominal surgery and previous biliary history. A significant difference (p-value < 0.05) in any of these factors between the two treatment groups will be considered to be an imbalance, the most important factors being APACHE-II score and age. Although we do not expect this to occur, results within the treatment groups will be stratified according to APACHE-II score and age to assure reliable results.

For nominal data the Chi-Square test will be used. For continuous data and counts the independent sample t-test or one-way ANOVA will be used.

In the interim analysis (after one year) the occurrence of the primary endpoint will be compared between the two treatment groups. After the one year follow up of the last patient is completed primary as well as secondary outcomes will be analyzed and compared.

Results will be presented as odds ratios with a corresponding 95% confidence interval. A two-tailed P < 0.05 is considered statistically significant.

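### Difficulty of cholecystectomy falls under the general between-arm comparison, but in the drainage arm the score exists only for a minority selected after randomisation

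*Protocol article*

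**What the plan says.** The secondary endpoints in the section Primary & Secondary endpoints include "difficulty of cholecystectomy (as scored by VAS 1-10"). The Analyses section sets three general rules and makes no exception for this endpoint:

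- "All patients will be analysed according to the intention to treat approach".
- "For continuous data and counts the independent sample t-test or one-way ANOVA will be used".
- After one-year follow-up of the last patient, "primary as well as secondary outcomes will be analyzed and compared".

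The Treatment protocol section decides who can have a score. Group A is allocated to cholecystectomy, to be done within 24 hours of randomisation. In group B one route to cholecystectomy is stated. It is failure of drainage, defined as clinical deterioration, persisting fever, or "increasing infection parameters < 48 hours despite accurate drain position and function will lead to LC". Otherwise "The drain will be left in situ during a period of three weeks", is then imaged and removed, and no cholecystectomy is scheduled.

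The Background reports the sponsor's retrospective series of 27 PC patients: "The success rate was 92.6% (N = 25"), and, over a mean follow-up of eight weeks, "four patients underwent an interval cholecystectomy".

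Two other places describe the item more broadly. The Abstract refers to the difficulty of procedures in general. Data collection & follow-up has the surgeon or the radiologist score difficulty straight after the procedure.

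**The concern.** Difficulty of cholecystectomy is defined only for patients who have one. In the LC arm that is nearly everybody, by allocation. In the PC arm, having a cholecystectomy is itself a consequence of how the allocated treatment went. Applied to this endpoint, the general rule sets an almost complete randomised arm against a subset of the other arm chosen by a post-randomisation event. Intention to treat cannot hold when most of one arm has no value and those who have one are selected.

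At stake is how the result is read. A difference in mean score could be reported as an effect of drainage on the difficulty of later surgery, harder or easier, when selection alone could have produced it.

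**Working it through.** The document gives no figure for this endpoint, so there is none to reproduce. The check has two steps: how many PC patients would have a score, and what selection can do to the planned test.

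**Step 1: who has a score.** The evaluable size is 140 per arm (Sample size calculation). The sponsor's series (Background) gives 25/27 successes, hence 27 − 25 = 2 failures, and 4 interval cholecystectomies.

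- Failures only: 2/27 = 7.4%; 140 × 2/27 ≈ 10.
- Interval cases only: 4/27 = 14.8%; 140 × 4/27 ≈ 21.
- Both, if they do not overlap and all are operated on: 6/27 = 22.2%; 140 × 6/27 ≈ 31.

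On these inputs about 78% (1 − 6/27) to 93% (1 − 2/27) of the PC arm would have no value, against nearly complete data in the LC arm.

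**Step 2: what selection can do.** The following assumptions are not in the documents: no true treatment effect, difficulty standardised to SD 1, and correlation ρ between a patient's severity and the difficulty score. If the most severe fraction f of the PC arm is operated on, then approximately

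shift = ρ × φ(c)/f, with c the upper-f point of the standard normal and φ its density;

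SE = √(1/140 + 1/m), with m = 140f.

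Example with f = 4/27 and ρ = 0.3: c = 1.044, φ(c) = 0.231, so shift = 0.3 × 0.231/0.148 = 0.47 SD. SE = √(1/140 + 1/20.7) = 0.235. The ratio is about 2.0, so a two-sided 5% test rejects in about 51% of trials.

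Simulating the t-test with 140 LC patients and different selection rules in the PC arm gives the rejection rates below (nominal 5%):

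| Who is operated on in the PC arm | ρ = 0.2 | ρ = 0.3 | ρ = 0.5 | Shift in SD, ρ = 0.2 to 0.5 |
|---|---|---|---|---|
| 21 or 31 most severe | 25-27% | 50-53% | 92-94% | +0.27 to +0.77 |
| 10 most severe plus 21 at random | 8% | 12% | 23-24% | +0.10 to +0.25 |
| 10 most severe plus 21 least severe | 7% | 9% | 15% | −0.09 to −0.22 |
| 31 chosen with correlation 0.3 to severity | 7% | 9% | 17% | +0.08 to +0.20 |

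With ρ = 0 the rate stays at 5%. The excess therefore comes entirely from selection. Its size and sign depend on who is operated on and on ρ, and the documents fix neither.

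**The case against.** **The comparison is stated only in general terms.** No sentence assigns a test, a contrast or an analysis set to difficulty, and an analysis plan that is not shown may treat it separately. A reader might infer that the sponsor has committed to a t-test on this very score. The article does not go that far, and this part of the objection stands. What remains is that the article states a rule covering all secondary outcomes, names an endpoint the rule cannot fit, and makes no exception. That is more than a detail left for later.

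**The large rejection rates are near a worst case.** A reader might infer from the first row of the table that a false finding is likely. The documents do not support that. That row needs every operated PC patient to come from the most severe end, and nothing in the Background says the interval cases were the sickest; they may have been the fittest. Mixed or weaker selection gives about 7-24%, with a shift of either sign. For the same reason the documents do not support saying that the bias would make surgery after drainage look harder.

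**The counts are loose.** The Background does not say that the two failures were operated on, or that they are distinct from the four interval cases. Interval surgery is not a scheduled step in the protocol. The series had a median age of 83, was selected for PC, and was followed for eight weeks on average against one year here. The range 10 to 31 shows the order of magnitude; it does not forecast this trial.

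**The wider wording might rescue the endpoint.** Under the Abstract and the data-collection text, each PC patient could also have a score for the drain placement. But the endpoint as listed is specific to cholecystectomy, and a score for placing a drain is not the same outcome as a score for removing a gallbladder.

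**Conclusion.** The point holds, at minor severity. Under the general rule in the Analyses section, difficulty of cholecystectomy would be compared between nearly all LC patients and a minority of PC patients defined by a post-randomisation event. That comparison is not randomised, and intention to treat cannot be applied to it. This conclusion follows from the treatment pathways alone and needs no simulation.

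The size is uncertain. The counts rest on a small retrospective series carrying over, and the error rates on an assumed correlation and an assumed selection rule. The direction of any bias cannot be determined from the documents. The consequence is confined to one secondary endpoint: the primary endpoint, the sample size and the safety monitoring are not affected.

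**What to change.** Add one sentence to the Analyses section that exempts difficulty of cholecystectomy from the between-arm comparison. Report it descriptively among operated patients by setting (index LC, LC after failed PC, interval LC), with the number scored in each, and with no p-value or estimate presented as a randomised treatment effect.

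Align the wording in the Abstract and in Data collection & follow-up with the endpoint list. If difficulty of drain placement is also to be reported, list it as a separate descriptive item.

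The cost is a sentence and two small wording edits. No data are lost, and no visit, procedure or clinical rule changes.
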